### Data Collection and Management

Confirmed malaria case incidence data will be collected from public health facilities through electronic data capture. A REDCap (Research Electronic Data Capture; Vanderbilt University) database and mobile app were used for this study, and data synchronization will be performed daily for quality checking complemented with data queries distributed to the centralized data center at USTTB.

### A Priori Sample Size and Statistical Power

The power and sample size assessment is based on the ability to detect a clinically significant difference in malaria incidence proportions between the 3 comparison groups in year 1. The minimum clinically meaningful differences between the comparison groups was set at 10%. The sample sizes were calculated assuming a design effect of 2 with a 2-sided type I error set at 0.05 and power set at 80%. The number of required subjects per study arm for detecting at least 10% differences in malaria incidence proportions was 1552 in year 1. This result was inflated by 233 subjects in year 2 to account for new subjects due to increased child ages, yielding 1785 participants per arm total or 5355 participants overall.

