### Cluster Selection

A total of 9 villages were randomly selected from Mali’s Koulikoro District for participation. The selection strategy focused on 3 aspects: proximity to the Niger River (which lies in the southern part of the region) and the central and northern parts of the sampling region. Within these strata, villages were rank-ordered according to their populations. Random selection was carried out such that villages of high, medium, and low populations were sampled from each of these strata. A total of 3 villages (1 village per stratum with different ranking in terms of population size) were assigned to a single treatment arm (Figure 2).

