## Discussion

This study was designed to assess the effectiveness and efficacy of SP-AQ in children aged up to 9 years and of DHA-PQ as an alternative in the event of drug resistance to AQ or SP in West Africa and, more broadly, across Africa. The trial included 2 SMC regimens to provide a viable alternative therapy in the event of drug resistance or shortages in drug supply. The study enrolled over 5000 subjects in 9 villages in Mali’s Koulikoro District. The expanded phase of the study covered the entire Koulikoro District. The initial phase of the study covered 9 villages, which may be considered as a pilot for the larger district-wide trial.

This study provides an opportunity to directly measure the effect of the 2 drugs while extending SMC to older children in response to recent reports showing an age shift in malaria incidence and prevalence among older children. The study site here comprised different ecological settings represented countrywide with differential malaria transmission intensities. For instance, each study arm was composed of a village located along the Niger River where longer transmission seasons have historically occurred, a village located in the central part of Koulikoro District where malaria transmission peaks between July and October, and a village in the southern part of Koulikoro District where malaria transmission season has been historically shorter (August to November) than the other 2 locations. Also, all selected villages maintain community health facilities where malaria case management is done routinely. Additionally, a routine assessment of treatment compliance by measuring amodiaquine metabolite in the veinous blood of children after treatment will be performed for the first time to determine SMC compliance across all 4 dosing periods. While the number of villages was initially restricted to 3 per study arm, all 71 PHUs in Koulikoro will be covered across the 3 study arms should the study meet the go/no go criteria for continued funding.

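### The 80% year-1 power takes no account of having only 3 villages per arm; on the inputs that reproduce 1552 it is about 57–65% without a gain from blocking

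*Protocol article*

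**What the plan says.** All references are to the protocol article.

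- *A Priori Sample Size and Statistical Power* ties the calculation to differences between the comparison groups in year 1. The sample sizes were "calculated assuming a design effect of 2 with a 2-sided type I error set at 0.05 and power set at 80"%. On effect size: "The minimum clinically meaningful differences between the comparison groups was set at 10"%. The result is 1552 per arm, plus 233 in year 2, giving 1785 per arm and 5355 overall. The section gives no ICC, cluster size or baseline incidence with these figures and does not use the number of clusters.
- *Cluster Selection* fixes 9 villages: "A total of 3 villages (1 village per stratum with different ranking in terms of population size) were assigned to a single treatment arm". *Randomization* arranges them in a 3 × 3 Latin square of region by population size.
- *Hypotheses and Rationale* states both primary hypotheses within one age group: SP-AQ v no SP-AQ at 5–9 years, and DHA-PQ v SP-AQ under 5 years. The second is worded as absence of a statistical difference.
- *Discussion*: "The study site here comprised different ecological settings represented countrywide with differential malaria transmission intensities". Also: "The initial phase of the study covered 9 villages, which may be considered as a pilot for the larger district-wide trial".

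**The concern.** In a cluster-randomised comparison of two arms with 3 villages each, the error of the contrast is estimated from a handful of village-level values. A design effect enlarges the variance for clustering. It does not allow for the heavy-tailed reference distribution that applies when that variance is estimated from so few clusters. A normal-approximation formula with a flat design effect therefore overstates power at 3 v 3. A design effect of 2 spread over roughly 259 children per village and age group also leaves room for very little variation between villages.

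The second primary hypothesis raises the stakes. It expects DHA-PQ and SP-AQ not to differ statistically in the under-5s, and low power makes that result easier to obtain. A reader who trusts the 80% may take a null result from 9 villages as support for similarity.

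**Working it through.** **1. Reproduce the plan's figure.** From the article: two-sided alpha 0.05, power 80%, difference 10%, design effect 2. Inferred: rates of 50% v 40% (10 points, absolute) and a doubling for two age groups per arm.

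n = [1.960·√(2·p̄·q̄) + 0.842·√(p1q1 + p2q2)]² / d²

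With p̄ = 0.45, p1q1 + p2q2 = 0.25 + 0.24 = 0.49 and d = 0.10:

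n = (1.379 + 0.589)² / 0.01 = 387.3, rounded up to 388.

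388 × 2 (design effect) = 776 per age group per arm; 776 × 2 (age groups) = 1552. This matches exactly. The rest follows: 15% of 1552 is 232.8, or 233; 1552 + 233 = 1785; 1785 × 3 = 5355.

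**2. What design effect 2 implies.** Children per village and age group: m = 776 / 3 = 258.7.

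ICC = (DE − 1)/(m − 1) = 1/257.7 = 0.0039. Between-village SD = √(0.0039 × 0.45 × 0.55) = 0.031, about 3 percentage points.

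**3. Power at the plan's own design effect, 50% v 40%.**

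SE = √(DE × 0.49 / 776) = √(2 × 0.49 / 776) = 0.0355; noncentrality = 0.10 / 0.0355 = 2.81.

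| Reference | Critical value | Power |
|---|---|---|
| Normal | 1.96 | 80% |
| t, 6 df (error pooled over 9 villages, 3 arms) | 2.45 | 65% |
| t, 4 df (3 v 3 villages) | 2.78 | 57% |
| t, 2 df (full Latin-square residual) | 4.30 | 35% |

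No row credits blocking with removing variance.

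**4. Credit for region blocking (4 df with 9 villages).** The share of between-village variance removed is an assumption. If half goes, DE falls from 2 to 1.5, SE = 0.0308, noncentrality = 3.25 and power is about 68%. If all goes, DE = 1, SE = 0.0251, noncentrality = 3.98 and power is 84%.

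**5. Larger ICCs (assumed; the article gives none), 50% v 40%, no blocking gain.** DE = 1 + 257.7 × ICC.

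| ICC | DE | Power, normal | Power, 4 df |
|---|---|---|---|
| 0.01 | 3.6 | 56% | 36% |
| 0.02 | 6.2 | 36% | 24% |
| 0.05 | 13.9 | 19% | 13% |

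**6. Other baseline rates, 776 per group, design effect 2, 4 df.** 40% v 30%: 60%. 30% v 20%: 68%. 20% v 10%: 83%, falling to 60% at ICC 0.01.

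**The case against.** **The inputs are inferred.** This stands. The article gives neither 50% v 40% nor the age-group doubling, and does not say whether its 10% is absolute or relative. A relative 10% reduction from about 68% also gives roughly 776 × 2 = 1552 with no doubling, and an implied ICC of about 0.0019. The shortfall survives that reading: inputs sized to 80% by the normal formula give about 57% on 4 df. If all 1552 served one 50% v 40% comparison, 4-df power would be 84%, but those inputs require only 776 per arm at design effect 2 and do not match the age-specific hypotheses.

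**The villages differ by design, and the design balances it.** This largely stands. A reader might infer from the *Discussion* that varying transmission intensity proves an ICC above 0.004. The variation described there lies mainly between regions, and each arm has one village from each. Variation balanced across arms need not enter a stratified contrast, so the text does not show how large the residual variation is. Blocking could lift power as in step 4. For the same reason the 2-df figure of 35% should not be quoted alone: it charges the loss of degrees of freedom without crediting any variance removed.

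**The arithmetic is right.** It is. The fault lies in what the formula leaves out.

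**Further inferences not supported.** A reader might conclude that the trial's tests will be anticonservative, or that unequal village sizes push the design effect above 2. The article names no test, and nothing shows that its flat design effect excludes unequal sizes.

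**The larger phase solves it.** Only in part. The expansion to 71 health posts adds clusters, but the power statement is tied to year 1 and none is given for that phase.

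**Conclusion.** The concern holds in limited form. The stated 80% depends on a normal critical value that 3 villages per arm do not support. On the inputs that reproduce 1552, at the plan's own design effect, year-1 power is about 57–65% without a blocking gain. It is about 68% on 4 df if region blocking removes half of the between-village variance, and it exceeds 80% only in favourable cases (20% v 10%, or near-complete removal). It is lower if the ICC is above about 0.004, for example about 36% (4 df) at 0.01.

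The range rests on the inferred 50% v 40% rates and the inferred split by age group; ICCs of 0.01 and above and the blocking shares are assumptions. It would be too strong to say that the power is 57%, or that 80% cannot be reached under any inputs: baseline incidence and residual between-village variance are not given.

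**What to change.** 1. Keep the a priori calculation on record, and add that it ignores the number of clusters.
2. Restate year-1 power from 3 clusters per arm, with an explicit ICC, a t reference with its degrees of freedom, and stated baseline rates. Show a range: about 57–65% at 50% v 40% and design effect 2 without a blocking gain, and lower at larger ICCs. State any assumed gain from blocking.
3. Interpret years 1–2 as the pilot that *Results* and *Discussion* already call them, and say that a non-significant DHA-PQ v SP-AQ difference there is not evidence of similarity.
4. Report power or precision for the 71-post phase separately, from the actual number of randomised units after adjacent posts were merged.

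The confirmatory test should not be moved to the larger phase on this ground now. Data collection has ended and preliminary findings from both phases are reported, so the move would be post hoc.

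The cost is restated figures and a paragraph of interpretation, with no extra children. The downside is a less favourable power figure and a softer claim from years 1–2.

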### Phase 2 (Years 3-5, 2021-2023)

This phase involved expansion to 71 public health posts in years 3-5 (Figure 3). The district-wide data collection plan will build on the efforts for years 1-2 and focus on (1) cluster-randomized health posts to the 3 treatment arms and (2) semiannual community cross-sectional surveys. More specifically, the 71 health posts over the entire district were divided into 4 regions (Table 2).

**Figure 3 figure3:**
[figure not shown]
Map of the selection approach for 71 public health posts in Mali’s Koulikoro District.

**Table 2 table2:** Stratum matched by the year of the study.

Stratum (region), years 3-5 sampling approach	Stratum (region), years 1-2 sampling approach
Northeast	Not done
Northwest	North
Southwest	Central
Southeast	South

Within the stratum, health posts will be randomized to 1 of 3 treatment arms (SP-AQ <5 years, SP-AQ <10 years, and DHA-PQ <10 years). Allocation was proportional to population size based on census populations up to 9 years of age while balancing on population sizes across the 3 study arms. For regions maintaining a total number of health posts that were not divisible by 3, 1 or 2 adjacent health posts were considered as a single unit to ensure divisibility (Figure 3).

The health facilities selected in years 1 and 2 were also be selected in years 3-5 and will leverage the process and training already in place in 9 health centers. Patterns over the entire 5-year study period will be analyzed for these 9 villages. Semiannual cross-sectional household surveys will permit assessment of community-level effects over the entire 5-year period.

## Results

The study began on July 1, 2019. Through November 2022, a total of 4556 children were enrolled during the pilot phase (2019-2020) in 9 villages across the Koulikoro Health District. In 2022, preliminary findings have been presented at the American Society of Tropical Medicine Conference [16] and published in the *American Journal of Tropical Medicine and Hygiene* [17]. SP-AQ and DHA-PQ were highly effective in reducing *P falciparum* malaria in children 5-9 years in Koulikoro, Mali, at both the pilot and district-wide study phases. Data collection ended in spring 2023, and the findings are expected to be published later in early 2024. Results will be summarized and reported using both intention-to-treat and per-protocol analyses.

## Discussion

This study was designed to assess the effectiveness and efficacy of SP-AQ in children aged up to 9 years and of DHA-PQ as an alternative in the event of drug resistance to AQ or SP in West Africa and, more broadly, across Africa. The trial included 2 SMC regimens to provide a viable alternative therapy in the event of drug resistance or shortages in drug supply. The study enrolled over 5000 subjects in 9 villages in Mali’s Koulikoro District. The expanded phase of the study covered the entire Koulikoro District. The initial phase of the study covered 9 villages, which may be considered as a pilot for the larger district-wide trial.

This study provides an opportunity to directly measure the effect of the 2 drugs while extending SMC to older children in response to recent reports showing an age shift in malaria incidence and prevalence among older children. The study site here comprised different ecological settings represented countrywide with differential malaria transmission intensities. For instance, each study arm was composed of a village located along the Niger River where longer transmission seasons have historically occurred, a village located in the central part of Koulikoro District where malaria transmission peaks between July and October, and a village in the southern part of Koulikoro District where malaria transmission season has been historically shorter (August to November) than the other 2 locations. Also, all selected villages maintain community health facilities where malaria case management is done routinely. Additionally, a routine assessment of treatment compliance by measuring amodiaquine metabolite in the veinous blood of children after treatment will be performed for the first time to determine SMC compliance across all 4 dosing periods. While the number of villages was initially restricted to 3 per study arm, all 71 PHUs in Koulikoro will be covered across the 3 study arms should the study meet the go/no go criteria for continued funding.

Particular challenges at the outset of the study planning involved garnering support from regional health administrators about using DHA-PQ instead of SMC and extending SMC use to children aged 5-9 years. Since the inception of Mali’s NMCP, a key partner in this effort made apparent the study’s rationale in terms of its implications on potential drug resistance with health agents, community leaders, and health workers before the SMC campaign was launched in Mali. Determining the appropriate age target for preventive therapies remains challenging for developing countries like Mali. The age captured during the most recent census was used to estimate the number of children failing in the <5 and 5-9-year age groups, which was usually reported by the participants’ parents or guardians. However, approximately 2% of subjects were misclassified during the SMC administration due to erroneous reporting during the census. Therefore, more accurate estimations of participant age (which was used to define the comparison groups) were captured for the study here at baseline.

SMC covers the rainy season that coincidentally occurs during school vacations and agricultural activities in rural Mali. Therefore, a child’s movement during that period is often a cause for losses to follow-up as children frequently might travel to Mali’s capital city of Bamako from July to September, while others will move with their family to the farms (hamlets) until October when school commences.

We believe that this study provides a somewhat novel study design that will aid researchers in assessing age targets in locations where controlled studies are not feasible.

## Appendix

Multimedia Appendix 1 Peer review report from the National Institute of Allergy and Infectious Diseases Special Emphasis Panel Limited Competition: Revision Applications for International Centers of Excellence for Malaria Research (NIH, USA).

## Abbreviations

ACT: artemisinin-based combination therapy
AQ: amodiaquine
DHA: dihydroartemisinin
ICEMR: International Centers of Excellence in Malaria Research
IPTp: intermittent preventive treatment of pregnant women
LLIN: long-lasting insecticide-treated mosquito net
NMCP: National Malaria Control Program
PHU: public health unit
PQ: piperaquine
REDCap: Research Electronic Data Capture
SMC: seasonal malaria chemoprevention
SP: sulfadoxine-pyrimethamine
USTTB: University of Sciences, Techniques and Technologies of Bamako, Mali
WHO: World Health Organization
